### 11.3.3 Secondary outcome analysis

- Different sensitivity analysis will be done to evaluate the differences between the programs at 18 months post-randomisation. A linear regression model with %SS as outcome and type of program as a predictor will be considered with inclusion of other factors like gender, age at assessment, comorbidities, family history of stuttering and recovery of stuttering, baseline stuttering severity assessment (%SS and SR), and temperament (CBQ-short version). Linear regression assumptions will be checked and if needed transformations or other models will be explored. This analysis will be done in the per-protocol (naïve per-protocol) as well as in the intention-to-treat population. For the intention-to-treat population children who drop out from the study get the last recorded %SS carried forward.
- In the secondary analysis we will also consider the comparison between Mini-KIDS and SCBT.
- As %SS is measured repeatedly (3, 6, 9, 12, 18, 24, 60 months post-randomisation) we can consider a linear mixed model with child as random intercept to compare the evolution over time between the programs and to get an even more precise estimate of the difference at 18 months post-randomisation. The linear mixed model also allows the inclusion of confounders and also for this

model assumptions will be checked and if needed revised. This analysis will be done in the per-protocol as well as in the intention-to-treat population.

- SR (also averaged over home and treatment session sample), score on the KiddyCAT and EQ-5D-Y-proxy 1 at 18 months post-randomisation will be compared between the three programs using an analysis of variance and answers to the ISPP-questionnaire using a Chi-square test. These outcomes will also be studied in a multiple linear regression model (with confounders as mentioned before) with adjustment for their baseline values. The same analysis will be done for the EQ-5D-Y-proxy 1 scores at the long-term follow-up at 2 years and 5 years post-randomisation.
- For the continuous measures SR, EQ-5D-Y proxy 1, measured at different time points we can compare the evolution over time between the programs using a linear mixed model. This model also allows to look at differences at a specific time point in a post-hoc comparison. For the answers to the ISPP-questionnaire measured at different time points this can be done using a generalized linear mixed model. For the ordinal outcomes parent report about their PCWS's stuttering severity and their satisfaction about the PCWS's communication in everyday speaking situations depending on variability a linear mixed or generalized linear mixed model will be used.
- The number of weeks, the number of treatment sessions, the treatment time needed until the maintenance phase begins will be compared between the three programs using an ANOVA or Kruskal Wallis test as appropriate. This outcome will also be studied in a multiple linear regression model adjusting for possible confounders.
- We will look at the proportion of children that are successful (defined as  $<1\%$  SS and  $SR \leq 1$ ) at 18 months and at 5 years post-randomisation. They will be compared by a Chi-square test (or Fisher's exact test as appropriate) between the three programs. The time to reach success between the three programs will be compared with a Kaplan-Meier plot and analyzed using a Cox regression model with correction for confounders.
- %SS and SR at 18 months post-randomisation will be evaluated separately for the videos at home and for the videos recorded during the treatment sessions using linear regression models as described for the averages of the two samples.
- For the above analysis we will first consider the intention-to-treat population to preserve randomization, if necessary also per-protocol population will be considered.
- Safety analysis will be done in all patients that are randomised.
- Numbers of children who drop out and reasons for drop out, as well as leave the allocated treatment arm (numbers, reason and switched treatment) will be described per treatment. Numbers per program will be compared using a Chi-square test (or Fisher's exact test as appropriate). A time to drop-out analysis or a time to switch analysis will be performed in case  $> 10\%$  drop-out or a 10% switch was present in the trial.

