#### ***8.8.11 5-years post-randomisation data collection point (Follow-up)***

At the session + or – 4 weeks the 5-years post-randomisation data collection point, the CI and/or Co-CIs ask the parent to video record a conversation with the PCWS at home. The parent loads this onto a GDPR-proof

platform and labels the video recording according to the requirements. No treatment is provided during this conversation. The instructions for the video recording need to be followed.

Video analysts will score %SS and SR in the video recorded speech samples of the PCWS.

The parent is asked to complete the EQ-5D-Y proxy 1 on an electronic device (computer or smart phone) within 4 weeks before or after the data collection point. The parent is also asked to report on their child's stuttering severity based on a 10-point scale with three descriptors only and to report on the satisfaction of the PCWS's communication in everyday speaking situations based on a 9-point scale with two descriptors only. Access to the questionnaires is emailed to the parent.

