### 8.9.3 Video analysis: Rating of %SS and SR

The video analyst coordinator organises the video analysis process. The video analysts look at the videos that are uploaded onto a GDPR-proof platform to calculate %SS and assign a SR to the two video recordings (one from home and one from the treatment session) at each data collection point. An average of the two scores will be taken as outcome measure. Success of the intervention is frequently defined in terms of achieving <1% SS. To achieve such a low average, one must have very low scores in both speech samples (home and during the treatment sessions), so averaging the % SS is routine practice in the standard clinical care.

The video analysts will be able to access the video recordings without knowing which treatment approach the PCWS is receiving/has received. A list of the videos of the French-speaking PCWS (for the French-speaking video analysts) and a list of the videos of the Dutch-speaking PCWS (for the Dutch-speaking video analysts) will be generated without information about the treatment arm and the time on which the video is recorded. In each list, 5% of the video recordings will re-appear as those are intended to be rated by two video analysts to establish the interrater agreement (see further for detail about the interrater agreement analysis). This 10% of videos is clearly indicated on the list. The video analysis will commence 6 months after the start of recruitment. This 6-month waiting time is included to avoid bias for the baseline video recordings.

If a PCWS speaks another language than Dutch, French or English, the research team will use their network to search for a native speaker of the language spoken by the PCWS and parent. This person will be invited to help the video analyst with scoring the video.

Standardisation of the video analysts will be guaranteed by a manual and by a training in which three video recorded speech samples (other than TreatPaCS-videos) will be scored together with all video analysts for %SS and SR.

Quality of the ratings will be assured by an evaluation of five video samples of French-speaking PCWS performed by the French-speaking video analysts and five video samples of Dutch-speaking PCWS performed by the Dutch-speaking video analysts. In a meeting they will discuss the stuttering moments and come to a consensus.

For %SS, clear instructions will be provided, including:

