| Relapse reporting and relapse management                               |                           |                    |          |                                                                       | x*                                                                                                                               | x*                                            | x*                                             | x                                              | (x)                                |                                    |
| Risk assessment                                                        |                           |                    |          | x                                                                     | x                                                                                                                                | x                                             | x                                              | x                                              | x                                  |                                    |

Tx = Treatment; %SS = Percentage syllables stuttered; SR = Severity Rating; CAT = Communication Attitude Test; QOL = Quality of Life; CBQ = Children's Behaviour Questionnaire; ISPP = Impact of Stuttering on Preschoolers and Parents; \*: if applicable, that is, if treatment is not initiated straight away; \* if applicable, that is, if the child is in Maintenance Phase. (x) if applicable, that is, if the child is still seeing the SLT; Underlined & bold (18 months post-randomisation) = primary end point; \*\* performed by the video analysts; a depending on the treatment arm; ® Parent compliance and treatment fidelity checklists are completed for each treatment session; ® Treatment fidelity is also evaluated based on of video that is recorded for 20% of the PCWS (entire treatment session) at 1-, 3-, 6- and 12-months post-randomisation.

Figure 3. Overview of measurements in TreatPaCS

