## 11.1 Sample size calculation

In this trial the aim is to prove non-inferiority of Mini-KIDS compared to LP and SCBT compared to LP. The primary outcome is %SS at 18 months post-randomisation.

The non-inferiority margin was set at 1.0% SS following Bridgeman et al. (2016) and Donaghy et al. (2020). Several studies report a standard deviation on %SS at 18 months varying from 0.4 to 2.1 in different number of children (Arnott et al. 2014; Bridgeman et al. 2016; Donaghy et al. 2020; De Sonnevile-Koedoot et al. 2015). Pooling all these results (weighing them with the number of children per study) we estimated a value of 1.7 for the standard deviation at 18 months on %SS. We adjust the usual one-sided significance level of 2.5% to 1.25% because we are interested in the two comparisons (Mini-KIDS versus LP and SCBT versus LP).

Assuming that in reality there is no difference between the three programs and using a power of 90% and a one-sided significance level of 1.25% we need 73 children in each group to show non-inferiority. Taking into account a 11% dropout (de Sonnevile-Koedoot et al. 2015) we need to randomise 249 children in total (83 children per arm).

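### Carrying the last value forward, and a one-variance mixed model over months 3 to 60, give weak intention-to-treat support for the 18-month %SS contrast; the 5-year %SS is also a different measure

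*Protocol*

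**What the plan says.** The primary analysis (section 11.3.2) is an inverse-probability-weighted regression in the per-protocol population. Intention-to-treat results for 18-month %SS come from sections 11.3.3 and 11.3.4, by three routes:

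- A covariate-adjusted linear regression with a firm rule for missing values: "For the intention-to-treat population children who drop out from the study get the last recorded %SS carried forward".
- Multiple imputation, which section 11.3.4 says will be explored as an alternative and compared.
- An optional mixed model: "we can consider a linear mixed model with child as random intercept to compare the evolution over time between the programs". The visits listed are 3, 6, 9, 12, 18, 24 and 60 months. One stated aim is a sharper 18-month difference. Assumptions are to be checked and the model revised if needed. Section 11.3.4 regards missing at random as reasonable for this model.

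On the measure itself, %SS comes from a home and a treatment-session recording: "An average of the two scores will be taken as outcome measure" (section 8.9.3, and section 4.3.1 for the primary endpoint). At 5 years, section 8.8.11 has the investigators only "ask the parent to video record a conversation with the PCWS at home", and Figure 3 shows no session sample at that point. At 2 years, Figure 3 brackets the session sample, and its footnote explains the bracketed mark as "x) if applicable, that is, if the child is still seeing the SLT". Section 8.8.10 describes both 2-year samples without that condition. Success (%SS below 1 and SR at most 1) is evaluated at 18 months and at 5 years.

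**The concern.** Because the primary analysis is per-protocol, intention-to-treat is the check that keeps the randomised comparison. Three features weaken it.

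1. Section 2 expects near-zero stuttering by 18 months. A value recorded earlier, and on the wording possibly the baseline value, then overstates where a lost child would have been. This method is not valid under missing at random when the outcome is falling, although section 11.3.4 accepts that assumption. The trial is open-label and plans to compare dropout by arm, so unequal dropout is foreseen.
2. A child intercept alone imposes one variance on every visit. If the spread of %SS shrinks as children improve, the 18-month standard error is borrowed from noisier visits.
3. Values to 18 months average two recordings, while the 60-month value is one home recording. Section 8.9.3 defends averaging because a mean below 1 %SS needs low scores in both settings. At 5 years the same threshold is applied to one setting.

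**Working it through.** **Inputs from section 11.1.** "The non-inferiority margin was set at 1.0% SS"; "we estimated a value of 1.7 for the standard deviation at 18 months on %SS"; "using a power of 90% and a one-sided significance level of 1.25" per cent; true difference 0; 73 evaluable per arm; 11% dropout overall; 249 randomised (83 per arm). The protocol gives no dropout by arm, no %SS trajectory and no SD at other visits. Everything below that uses those is assumed.

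**The plan's own figure.** n = 2 × 1.7² × (2.241 + 1.282)² / 1.0² = 71.7, so 72 by the normal formula. With the t distribution, power at 73 per arm is 0.89996, i.e. 90%. Then 73 / 0.89 = 82.02, so 83 per arm and 249 in total. The sample size reproduces.

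**Carrying forward.** Let d be the dropout proportion and x the excess of the carried value over the child's true 18-month value.

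Shift in contrast (experimental − LP) = d_exp × x_exp − d_LP × x_LP

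The standard error with 83 per arm is 1.7 × √(2/83) = 0.264. One-sided error at the margin is Φ(−shift/0.264 − 2.241); power at no difference is Φ((1 − shift)/0.264 − 2.241). SD is held at 1.7.

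| Dropout LP / exp | Excess LP / exp | Shift | Error at margin | Power |
|---|---|---|---|---|
| 11% / 11% | equal | 0 | 1.25% | 94% |
| 11% / 11% | 1 / 3 | +0.22 | 0.1% | 76% |
| 11% / 11% | 3 / 1 | −0.22 | 8.0% | 99% |
| 16% / 6% | 1 / 1 | −0.10 | 3.1% | 97% |
| 16% / 6% | 4 / 4 | −0.40 | 23.4% | 99.9% |
| 6% / 16% | 1 / 1 | +0.10 | 0.4% | 88% |
| 6% / 16% | 4 / 4 | +0.40 | 0.01% | 51% |

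A milder case: 11% dropout in both arms, last visit equally likely at 3, 6, 9 or 12 months, both arms at 1.5 by 18 months. Assumed means at those visits are 3.2, 2.2, 1.8, 1.6 for LP and 4.0, 3.2, 2.6, 2.0 for a slower experimental arm. The excesses are 2.20 − 1.50 = 0.70 and 2.95 − 1.50 = 1.45, so the shift is 0.11 × 0.75 = 0.08. Simulation gave 0.076.

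**Random intercept.** With complete data and a separate mean for each arm and visit, the estimate at 18 months is the raw mean difference. Its standard error uses the average variance over all visits:

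SE ratio = root mean square of visit SDs / SD at 18 months

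- SD 1.7 at every visit: ratio 1.00.
- SDs 3.5, 2.8, 2.4, 2.0, 1.7, 1.7, 1.7 over months 3 to 60: √(38.52/7) = 2.346; 2.346/1.7 = 1.38.
- SDs 3.0, 2.6, 2.3, 2.0, 1.7 over months 3 to 18: 2.364/1.7 = 1.39; adding months 24 and 60 at 1.7 gives about 1.29.
- SD 1.7 at 18 months and 1.2 elsewhere: √((6 × 1.44 + 2.89)/7) = 1.283; 1.283/1.7 = 0.755.
- Falling to 1.7 from 2.5 or from 4.5 at month 3: 1.15 and 1.61.

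At 73 per arm, ratios of 1.15 to 1.61 cut power from about 90% to 83–48%, with error at the margin below 0.5%. A ratio of 0.76 raises that error to 4.5%.

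Forty simulated trials (SDs 3.0, 2.5, 2.2, 1.9, 1.7, 1.7, 1.7) gave a mean model standard error of 0.354, against 0.278 from the 18-month data alone. The two point estimates agreed to rounding error.

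**The measure by time point.** To 18 months: home and session, averaged. At 24 months: home, plus a session sample that is conditional in Figure 3 and unconditional in section 8.8.10. At 60 months: home only, for every child. Section 4.3.4 ends the trial at 2 years, so a model over months 3 to 60 cannot be completed when the trial ends.

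**The case against.** A reader might infer that the intention-to-treat result rests on carrying forward alone. It does not: multiple imputation is to be explored, and the mixed model uses all observed values without carrying forward. The rule also reaches only children lost to the study, since section 8.10.1 keeps those who merely stop treatment in follow-up. Both points stand and limit the size. But the imputation is not firmly committed to, and carrying forward is the only firm rule.

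A reader might also infer that the mixed model biases the 18-month contrast. With complete data and visit-specific means it does not, and a standard error that is too large makes a non-inferiority claim harder, not easier. The model is optional and carries a revision clause, and covariance detail is commonly left to a separate analysis plan. What remains is that the protocol states the structure and claims a gain in precision that the structure does not provide. Covariates could help, but the 18-month regression may use them too.

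The most tempting overstatement is that the 5-year arm comparison is confounded by recording location. It is not, because every child in every arm then has a home sample only. At 24 months, availability of the session sample could differ by arm, since expected treatment lengths differ. The documents do not establish this, and Figure 3 and section 8.8.10 disagree on whether the sample is conditional at all.

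Finally, home-only %SS and SR at 18 months are already to be analysed separately (section 11.3.3), and agreement between settings is to be explored (section 11.3.5).

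**Conclusion.** The concern holds as a weakness in the supporting analyses, not as a fault in the primary analysis or the sample size.

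- Carrying forward is a poor lead rule for a falling outcome. Its bias is zero with equal dropout and equal excess, about 0.08 in the milder case, and 0.1 to 0.4 %SS in either direction with 6% against 16% dropout and an excess of 1 to 4. All these inputs are assumptions.
- The single-variance model mis-sizes the 18-month standard error by a factor of about 0.76 to 1.61 across assumed SD patterns, and by nothing if the SDs are constant. The direction is not known in advance, so the promised precision does not follow.
- The 5-year success proportion is not on the same measure as the 18-month one. The documents give no home-to-session correlation, so I put no figure on the difference. The 5-year between-arm comparison is unaffected by recording location.

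**What to change.** 1. Make the lead intention-to-treat analysis of 18-month %SS a repeated-measures model on months 3, 6, 9, 12 and 18, with categorical visit, arm-by-visit terms, baseline %SS and unstructured within-child covariance. Multiple imputation under missing at random would also serve. Report the 18-month contrasts with the 97.5% confidence interval already planned. Categorical visit should be stated: in the simulated example above, a straight line in time over months 3 to 60 gave a contrast of about +0.4 where the truth was 0.
2. Add one sensitivity analysis for departures from missing at random. Drop carrying forward, or keep it only as a supplement.
3. Analyse 60-month %SS, SR and success separately on the home sample, and set them beside the home-only 18-month values already planned.
4. Reconcile section 8.8.10 with Figure 3 on whether the 2-year session sample is collected for all children. If it is not, use the home sample at 24 months.

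The cost is revised wording and a little extra analysis; no new data are needed.

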#### 4.3.2 Secondary endpoints

%SS (measured on video recordings by blinded video analysts) is also measured at 3, 6, 9, 12 months and 2 and 5 years post-randomisation.

SR (measured on video recordings by blinded video analysts) is measured at 3, 6, 9, 12, 18 months and 2 and 5 years post-randomisation. Whereas %SS measures the frequency of stuttering, SR measures frequency and severity. For example, a sentence spoken with one fixed posture with audible airflow (prolongation) combined with a non-verbal superfluous behaviour (e.g., grimace) will result in a higher SR than three monosyllabic repetitions.

%SS and SR (measured on video recordings by blinded video analysts) is measured at 18 months post-randomisation for the videos at home and for the videos recorded during the treatment sessions.

The proportion of children that are successful (defined as  $<1\%$  %SS and  $SR \leq 1$ ) is evaluated at 18 months and at 5 years post-randomisation.

%SS and SR are determined by blinded video analysts on the videos of the speech samples. Procedures are explained in section 8.8.

The impact of stuttering on PCWS and parents (ISPP) is measured at 3, 9 and 18 months post-randomisation. The quality of life (EQ-5D-Y proxy 1) is measured at 3, 9 and 18 months and 2 and 5 years post-randomisation. Communication attitude of the child (KiddyCAT) is measured at 18 months post-randomisation. These three measures assess the covert aspects of stuttering, as opposed to the overt aspects (measured by %SS and SR).

Parents are asked to report about their child's stuttering severity and their satisfaction with their child's everyday communication at 3, 6, 9, 12 and 18 months, 2 and 5 years post-randomisation.

The number of treatment time (in hours), number of weeks and number of treatment sessions are counted until the start the maintenance phase of each treatment approach.

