## **5 TRIAL DESIGN**

This study is a three arm, 1:1:1 randomised, open-label pragmatic comparative trial comparing Mini-KIDS, SCBT and the LP.

To show non-inferiority of Mini-KIDS compared to LP and SCBT compared to LP a parallel group design will be used. Stratified randomisation will be used according to site (30 sites) and gender.

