- Scores on the KiddyCat (PCWS' attitude towards his/her speech, 12 questions that the SLT poses to the PCWS, Appendix 4). Consent to use the questionnaire in the eCRF for research purposes was obtained from the editor (Sig vzw). The SLT notes down the answers and puts the information in the eCRF straight after the baseline session.
- The information form for the PCWS. The SLT informs the PCWS at the child's language level and signs the form.
- Scores on the QOL (EQ-5D-Y proxy 1, six questions that the parent(s) rate how they think the PCWS would rate his/her own state if s/he were asked directly and could communicate it, Appendix 5). Consent to use the questionnaire in the eCRF for non-commercial purposes was obtained from the editor (Euroqol). This questionnaire is provided digitally and the parent(s) answers the questions on a digital device (computer, smart phone).
- Scores on the CBQ-short version (temperament, 94 questions that parent(s) rate about their PCWS, Appendix 6). Consent to use the questionnaire in the eCRF for research purposes was obtained

from the editor (Bowdoin College). This questionnaire is provided digitally and the parent(s) answers the questions on a digital device (computer, smartphone).

- The ISPP-questionnaire (Impact of Stuttering on Preschoolers and Parents, 20 questions that parent(s) answer about their child, Appendix 7). Consent to use the questionnaire in the eCRF for research purposes was obtained from the authors (Langevin, Packman & Onslow). This questionnaire is provided digitally and the parent(s) answers the questions on a digital device (computer, smart phone).
- Parent report on the PCWS's stuttering severity (Onslow et al., 2021) and satisfaction of communication in everyday speaking situations (based on but adapted from Karimi et al., 2018) (Appendix 8).

Completing these parent questionnaires was timed and is estimated at 1 minute for the QOL (EQ-5D-Y proxy 1), 13 minutes for the CBQ-short version, 10 minutes for the ISPP and 1 minute each for the stuttering severity and the satisfaction of the child's everyday communication.

The participating SLT also adds the information from the screening to the e-CRF:

- Answers to the Anamnesis form (Appendix 3). The SLT took notes (on paper or electronically) during the screening/ baseline session and puts the data in the eCRF straight after the baseline session.

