## 11.3 Statistical analysis plan

### 11.3.1 Summary of baseline data and flow of patients

- Compare demographics like age, gender, comorbidities (Autism Spectrum Disorder, ADHD, language disorders...) and parent profile between the three programs. Means and standard deviation per group will be reported for age. For gender and comorbidities numbers and percentages are reported.
- Compare the stuttering state at baseline between the three programs using stuttering severity score (%SS) and the stuttering onset questionnaire. For the continuous variables means and standard deviations are reported (in case of skewness median and interquartile range are reported). For the categorical variable numbers and percentages are reported.
- Comparing the different questionnaires at baseline between the three programs (KiddyCat, EQ-5D-Y proxy 1, CBQ-short version, parent report about PCWS's stuttering severity and about their satisfaction of the PCWS's communication in everyday speaking situations). Means and standard deviations are reported (or median and interquartile range as appropriate). For the answers to the ISPP-questionnaire, frequencies and percentages are reported per program.

- A consort flow diagram will be produced to get an overview of the number of patients available at each stage: eligibility, randomisation, allocation, discontinuation and follow-up.

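### The ISPP outcome is given both a Chi-square test on its answers and a linear regression, but no ISPP variable is defined to which both could apply

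*Protocol*

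**What the plan says.** The ISPP is a secondary endpoint of the protocol: "The impact of stuttering on PCWS and parents (ISPP) is measured at 3, 9 and 18 months post-randomisation" (section 4.3.2). Section 8.6 describes it as "20 questions that parent(s) answer about their child". Section 14.3.3 records that one patient representative suggested adding it.

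Section 11.3 mentions the ISPP in four places:

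- Baseline summary (11.3.1): "For the answers to the ISPP-questionnaire, frequencies and percentages are reported per program".
- Comparison at 18 months (11.3.3): "answers to the ISPP-questionnaire using a Chi-square test". The same sentence gives SR, KiddyCAT and EQ-5D-Y an analysis of variance.
- Adjusted analysis (11.3.3, next sentence): "These outcomes will also be studied in a multiple linear regression model", with confounders and the baseline values. The outcomes it refers back to include the ISPP.
- Course over time (11.3.3): "For the answers to the ISPP-questionnaire measured at different time points this can be done using a generalized linear mixed model".

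Sections 4.2, 4.3.2 and 11.3 define no ISPP summary and give no rule for multiple items. The only significance level in the protocol belongs to the primary comparison (11.1): "We adjust the usual one-sided significance level of 2.5% to 1.25% because we are interested in the two comparisons".

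**The concern.** Two consecutive sentences of section 11.3.3 treat the ISPP as two different kinds of variable. The first needs categorical answers. The second needs a numeric value at baseline and at 18 months, and the protocol never says what that value is. An analyst would have to choose, possibly with the data in hand, whether to analyse items, a total or a selected question.

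The Chi-square is also a weak choice as the lead comparison. One Chi-square test cannot compare 20 different questions across three programs, so the sentence most naturally means one test per question. That could give up to 20 uncorrected p-values for one endpoint and leave room to highlight a chance item. Each such test disregards the child's baseline answer and any ordering of the response levels.

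**Working it through.** **Figures in the plan.** The protocol gives no figure for the ISPP analysis, so there is none to reproduce. Its only related calculation is the primary sample size. With margin 1.0, SD 1.7 and one-sided 1.25%, the noncentral t gives power 0.900 at 73 per arm. Then 73/(1 − 0.11) = 82.02, rounded up to 83, and 3 × 83 = 249. This agrees with section 11.1, and the ISPP plays no part in it.

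**Step 1: the passages side by side.**

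| Place | Scored instruments | ISPP |
|---|---|---|
| 11.3.1, baseline | KiddyCAT, EQ-5D-Y: mean and SD, or median and IQR | frequencies and percentages |
| 11.3.3, 18 months | SR, KiddyCAT, EQ-5D-Y: analysis of variance | Chi-square |
| 11.3.3, adjusted | linear regression with baseline | the same linear regression |
| 11.3.3, over time | SR, EQ-5D-Y: linear mixed model | generalized linear mixed model |

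Three rows keep the ISPP apart from the numeric outcomes. The adjusted-analysis row puts it among them.

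**Step 2: chance of a false item difference, independent items.** Inputs: 20 questions (section 8.6), three arms (section 5) and 5% per test. The 5% is an assumption, because no level is stated for secondary outcomes.

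P(at least one) = 1 − (1 − 0.05)^20 = 1 − 0.95^20 = 0.642.

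Under independence this first exceeds one half at 14 tests (0.512; 13 tests give 0.487). With other assumed levels, 20 tests give 1 − 0.975^20 = 0.397 and 1 − 0.9875^20 = 0.222.

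**Step 3: correlated items.** The documents give no item correlation, so a range is assumed. For yes/no items in three arms, each Chi-square has 2 degrees of freedom. Simulating 20 equicorrelated statistics of this kind (40,000 draws) gives:

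| Assumed item correlation | P(at least one) |
|---|---|
| 0 | 0.64 |
| 0.2 | about 0.59 |
| 0.4 | about 0.49 |
| 0.6 | about 0.37 |

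**Step 4: a second set-up.** Whole three-arm tables were simulated with 73 or 83 children per arm, yes/no and three-category items, and 4,000 replicates per setting. Here the correlation was set on an underlying normal scale. The ranges were 0.59–0.63 at 0.3, 0.53–0.57 at 0.5, 0.48–0.54 at 0.6 and 0.37–0.46 at 0.8. For answers split at the median, observed correlation = (2/π) × arcsin(underlying correlation), so 0.3, 0.6 and 0.8 correspond to 0.19, 0.41 and 0.59. On that scale the two simulations are compatible.

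**Step 5: after a change.** One pre-specified summary tested once at 5% has a 5% false-positive rate. If the items stay as tests, 0.05/20 = 0.0025 per item gives 1 − 0.9975^20 = 0.049 under independence.

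**The case against.** The strongest reply is that the protocol nowhere says the items are tested separately and nowhere rules out a total. Section 11 defers detail to a separate statistical analysis plan, where scoring and multiplicity for a secondary questionnaire usually belong. This stands in part. Item-by-item testing is a strong inference, not stated text, and the lack of a multiplicity rule is not in itself a fault of the protocol. It does not remove the clash between the two sentences that the protocol does contain.

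A single yes/no answer could be coded 0/1 and put through a linear model. The protocol does not say so, and choosing a generalized model for the same answers over time points the other way.

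A reader might infer that a false item difference is more likely than not. The documents do not support that. The 5% level is assumed, and answers from one parent about one child are likely to be correlated. At item correlations of 0.4 and 0.6 the figure is about 49% and 37%.

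A reader might also infer that baseline is ignored altogether, or that a consistent shift across items goes untested. That is too strong as well. The regression is planned with baseline adjustment, and the generalized linear mixed model could be specified to capture such a shift. The fair statement is that neither yields a defined ISPP result until the variable is named.

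**Conclusion.** The point holds as an internal conflict and a poorly chosen lead test. Section 11.3.3 assigns a Chi-square on answers and a linear regression to the same outcome, and no numeric ISPP variable exists to reconcile them.

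The size is conditional. If the 20 items are tested separately, uncorrected and at 5%, the chance of at least one false difference at 18 months is 64% under independence and about 37% to 59% at item correlations of 0.6 to 0.2. Even the lower end is about seven times the nominal 5%. These figures rest on the item-wise reading, the assumed 5% level and the assumed correlations.

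Severity is minor. The ISPP is one of many secondary outcomes, and no success rule, non-inferiority conclusion or sample size depends on it.

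**What to change.** In section 11.3.3, name one pre-specified ISPP summary as the ISPP endpoint at 18 months. It must suit the instrument's response options, which could not be checked because the content of Appendix 7 is not shown. A count of items showing negative impact is one possibility. Separate child and parent summaries are another, if a single total is not meaningful.

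Replace the Chi-square with the baseline-adjusted regression already planned, applied to that summary. Report differences with confidence intervals for Mini-KIDS versus LP and SCBT versus LP, and keep the planned Mini-KIDS versus SCBT comparison. Use the same variable in the model over time. Report individual items descriptively, or with a multiplicity correction if they are tested.

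The cost is a few sentences in the protocol or the statistical analysis plan before database lock, with no new data or visits. The drawback is that an equal-weight summary may hide effects confined to particular items, which the descriptive item table would partly offset.
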